### **3. PRELIMINARY STUDIES**

Our research team has pioneered investigations in ED-based HIV testing since 2004, and recent work has impacted HIV testing practices in the United States. The overarching goal of our work is to evaluate HIV testing models in the ED and to combine scientific rigor with program evaluation to best inform processes and policies on a national level. Through a series of projects we have determined that:

- 1) Although nontargeted opt-out rapid HIV screening is associated with newly-diagnosed HIV infection in the ED, the absolute number of patients identified is modest and most patients are identified late in their disease course. A large number of HIV tests have to be performed to identify a relatively small number of new HIV diagnoses, suggesting that many patients are missed with this approach, findings which have recently been confirmed by others. We also conclude that nontargeted screening does not adversely affect ED processes of care, and is more costly per new diagnosis than diagnostic testing.
- 2) When integrating nontargeted rapid HIV screening into a computerized kiosk system during triage, a large number of patients agree to rapid HIV testing when using an opt-out consent method in an ED setting; however, a larger proportion of those who accepted testing actually completed testing when an opt-in approach was used. Furthermore, and perhaps most importantly, patient understanding of HIV screening using opt-out consent is poor when compared to opt-in consent, and that the use of opt-in consent should be considered the approach for obtaining consent because it results in very little misunderstanding. Despite this, in order to be consistent with CDC recommendations, we will use an opt-out consent approach in this study with added consent confirmation to mitigate patient misunderstanding.
- 3) The use of an empirically-derived, externally-validated risk-based instrument, the Denver HIV Risk Score (DHRS), accurately categorizes patients into groups with increasing probability of HIV infection, and when implemented in an urban ED setting is associated with new HIV diagnoses when compared to nontargeted screening. In a single-center pilot comparison of the DHRS to nontargeted screening, we found that while both HIV screening methods identified the same absolute number of newly-diagnosed patients, significantly fewer tests were required when using the DHRS to target patients for screening. The DHRS was refined further and externally validated using a national HIV testing cohort. In this study two items related to specific sexual behavior (receptive anal intercourse and

vaginal intercourse) were removed in order to create a more succinct and easier to implement risk assessment tool. This refined DHRS performed similarly to the original DHRS.

## 4. METHODS

### A. Study Design

#### Specific Aim 1

For this aim, we will perform a multi-center, prospective, randomized, controlled clinical trial to evaluate the effectiveness of three distinct HIV screening approaches. Implementation of a randomized controlled trial will incorporate use of “pragmatic” or effectiveness methodologies, and will allow us to compare

[figure not shown]

the effectiveness of the three screening approaches while minimizing threats to internal validity. Patients will be screened using one of three interventions in a 1:1:1 random sequence; patients will therefore be offered HIV testing based on the results of which screening arm they are assigned, and in the case of the two screening tools, the results of risk assessment. All screening methodologies will be integrated into electronic patient triage systems at each site; as such, the actual randomization process will also be integrated into the electronic system, allowing for real-time concealed random allocation (**Figure 1**). Nurses who perform screening and all ED staff (e.g., physicians, nurses, and technicians) will understand the conceptual goals of the project but will be blinded to the specific hypotheses, and patients will be completely blinded to the purpose of the study.

All of the participating sites have established ED-based HIV testing programs, and all of the testing procedures that occur after patients are identified for HIV testing (i.e., consent for the test, performance of the test, results disclosure, linkage to care, etc.) will have been integrated into clinical processes within each ED as standards of care. The specific interventions being evaluated in this

study relate only to how patients are identified for and offered HIV testing. The standard process used by the DHMC ED and the integration of the three study interventions is described by the “ED Rapid HIV Screening Workflow” figure (**Appendix**).

#### Specific Aims 2 and 3

For these aims, we will perform prospective cohort studies nested in the clinical trial described above.

## **B. Settings**

This study will be performed in the EDs at: (1) Denver Health Medical Center (DHMC) as part of Denver Health and Hospital Authority in Denver, Colorado; (2) Highland Hospital as part of Alameda Health System in Oakland, California; (3) Johns Hopkins Hospital as part of Johns Hopkins University in Baltimore, Maryland; and (4) University of Cincinnati Medical Center in Cincinnati, Ohio. These sites were selected because of their heterogeneity of populations served, including a large proportion of underserved, racial and ethnic minorities, and adolescents; local HIV epidemics; geographic distributions in the United States; and expertise of investigators. DHMC will serve as the coordinating site for this project. However, each individual site will obtain approval from their respective Institutional Review Boards (IRBs). These approvals will be forwarded to the Colorado Multiple Institutional Review Board (COMIRB) when they are obtained.

## **C. Population**

### Criteria for Inclusion

Patients  $\geq 16$  years of age who present to the EDs during the study enrollment period will be eligible for inclusion if they are considered clinically stable by screening nurses or physicians and capable of providing consent for general medical care. Patients will be excluded from screening if they are: (1)  $< 16$  years of age; (2) unable to consent for care or HIV testing (e.g., altered mentation, critical illness or injury, etc.); (3) self-identified as infected with HIV; (5) victims of sexual assault; (6) presenting to the ED with occupational HIV exposure; or (7) eligible for the Fast-Track section of the ED where anticipated time in the ED is expected to be  $< 30$  minutes.

## **D. Interventions**

We will perform a prospective clinical trial at four institutions across the United States. Each study site will enroll consecutive eligible patients and randomize them to one of three rapid HIV screening interventions (described below), all of which are utilized as either local or national standards of care. The three screening interventions will be fully integrated into electronic patient screening and tracking systems in each ED and integrated into triage processes. Eligible patients will be screened by triage nurses in accordance with institutional standards of care; as part of this process, patients will be screened for HIV infection using one of the three screening tools in a 1:1:1 random sequence as determined by a random sequence generator built into the electronic patient screening systems. Patients will then be offered voluntary rapid HIV testing based on the screening arm they are assigned (i.e., patients randomized to the nontargeted HIV screening arm will be offered HIV testing without assessment of risk, whereas those randomized to the two targeted screening arms will be offered HIV testing only if they are identified as being at increased risk for HIV infection). To maximize generalizability to ED settings, screening will be performed 24 hours per day for the entire study enrollment period and all screening and testing methods will be fully integrated into ED operations.

### Specific Aim 1

#### *Intervention A: Nontargeted Rapid HIV Screening*

This screening arm will consist of nontargeted rapid opt-out HIV screening. Nontargeted HIV screening is currently the recommended approach by the CDC. Consecutive patients who present to the ED for evaluation, who meet criteria for inclusion, and are randomized to this arm will be offered voluntary, free,

and confidential rapid HIV testing by nurses using opt-out consent during medical screening. Patients who decline HIV testing during screening will be eligible for diagnostic HIV testing by their physicians.

### *Intervention B: Enhanced Targeted Rapid HIV Screening*

This screening arm will consist of implementing targeted rapid opt-out HIV screening using the refined DHRS to identify patients at increased risk for HIV infection (**Table 1**). Prior to initiation of this study, this approach was the standard of care in the ED at DHMC. The refined DHRS will be incorporated into electronic medical screening and patient tracking systems of each ED. As such, nurses will be able to electronically enter responses to each of the risk score questions during screening. In addition, using methodology already developed in Denver, the questions will be ordered to present potentially less sensitive questions before more sensitive questions, and each system will be developed to calculate a risk score real-time. A binary cut point was selected to define patients at increased risk (score  $\geq 30$ ) or not (score  $< 30$ ) based on results from our prior work and to simplify stratification when used by clinicians. More recent national external validation work supports this as the appropriate threshold. Patients identified as being at increased risk will be offered rapid HIV testing by nurses using opt-out consent. Patients identified as low risk will not be offered rapid HIV testing but will be eligible for diagnostic HIV testing by their physicians.

### *Intervention C: Traditional Targeted Rapid HIV Screening*

This screening arm will consist of implementing targeted rapid opt-out HIV screening using conventional risk behaviors to identify patients at increased risk for HIV infection. A Behavioral Risk Screening Tool

**Table 2.** Behavioral Risk Screening Tool (BRST) for identification of HIV infection.

**Please answer the following questions, “Have you ever...” OR if previously tested for HIV infection, “Since your last HIV test have you...” (Yes/No):**

1. Injected drugs and shared equipment with others (e.g., needles, syringes, cotton, water)?
2. Had unprotected intercourse with someone that you think might be infected with HIV (e.g., a partner who injected drugs, been diagnosed with an STD or hepatitis, had multiple or anonymous sex partners, or exchanged sex for drugs or money)?
3. Had unprotected vaginal or anal intercourse with more than one sex partner?
4. Been diagnosed or treated for an STD, hepatitis, or tuberculosis?
5. Have you ever been told you have an infection related to a ‘weak immune system’?

Any affirmative response of these questions is considered at increased risk for HIV.

(BRST), adapted from HIV testing recommendations from the CDC and World Health Organization dating back to 1987, will serve as a comprehensive list of behavioral risk associated with HIV infection

(**Table 2**). This form of targeted HIV screening was previously recommended by the CDC prior to 2006 and the USPSTF, but has never been systematically evaluated in an ED environment or compared to other, more contemporaneous, HIV screening methods. The BRST will be incorporated into the electronic medical screening and patient tracking systems in each ED using identical methodologies described for the refined DHRS (see Intervention B). Each of the 5 risk categories will be weighted equally so that the BRST score will range from 0 to 5. Nurses will apply the BRST to all patients who meet criteria for inclusion, and those who score  $\geq 1$  will be considered at increased risk for HIV infection and will be offered rapid HIV testing using opt-out consent. Patients who score 0 will be considered low risk for HIV infection and not offered rapid HIV testing; these patients will, however, be eligible for diagnostic HIV testing by their physicians.

*Diagnostic Rapid HIV Testing and Other HIV Testing Components*

Strengths of this study will be the inclusion of sites that use different implementation methods of HIV testing and linkage-to-care. Several stipulations, however, will be required of each site, including: (1) implementation and full integration of the interventions and HIV testing processes into the EDs; (2) use of streamlined opt-out consent (but in accordance with state statutes); (3) use of Food and Drug Administration (FDA)-approved rapid HIV testing to ensure timely and valid result reporting; (4) additional performance of clinician-directed diagnostic HIV testing for those patients not screened or who were identified as low risk during either of the 2 targeted interventions, or who declined testing when offered during any of the screening intervention; and (5) performance of confirmatory testing (using either Western blot or viral load assays) and appropriate linkage-to-care of those who test positive for HIV infection in the ED. Other operational features (e.g., which rapid tests are used, who performs prevention counseling, etc.) will not be explicitly stipulated during this study, although use of contemporaneous 4th generation HIV assays will be encouraged. Each institution has extensive experience performing rapid HIV testing in the ED and the methods that work at each site have been evaluated to ensure optimal patient care.

**E. Data Collection & Research Procedures**Specific Aim 1

During this aim, we will collect the following data elements for all eligible patients: (1) patient visit information (unique patient identifier, acuity level, mode of arrival, and date/time of visit); (2) demographics (age, sex, race/ethnicity, primary language); (3) payer information (commercial, Medicare, Medicaid, self, or state-sponsored); (4) details of randomization, including the intervention assigned and results of risk screening, if applicable; (5) whether a patient was offered, accepted, and completed rapid HIV testing; (6) results from all rapid HIV tests; and for all patients with at least one reactive HIV test; (7) results of confirmatory test results, additional behavioral risk information as collected during post-test counseling, initial CD4 counts and viral loads, whether they were successfully linked into care, and details of follow-up care and disease progression. Data from (1) through (5) will be collected prospectively using methods developed and validated in Denver from each institution's electronic screening, patient tracking, and laboratory reporting systems. Our study team has extensive experience interfacing with such systems and obtaining large amounts of valid patient-level data. Data from (6) and (7) will be retrospectively obtained using trained personnel and structured procedures. See **Data Dictionary, "Positive Patient Risk Information Data Collection Instrument"** and **"Longitudinal Data Collection Instrument" / "Limited Longitudinal Data Collection Instrument"** in the **Appendix**.

Specific Aim 2

During this aim, we will include randomly-selected time periods for which patients are included in this aim in an effort to ensure unbiased sampling. Direct program costs related to training, education, and implementation will be collected for each intervention at each study site. Program costs will include: (1) startup (computers, software, programming, and training); (2) personnel (administrative, ED, laboratory staff, and prevention counselors); and (3) supplies and equipment (informational sheets, HIV test kits, and blood draw supplies). Non-personnel costs will be obtained through expense reports. Personnel costs will be determined by trained research assistants by identifying position titles of those involved in each part of the interventions and collecting time-motion data using a structured data collection instrument. Time-motion data will be collected during randomly-selected time periods during patient enrollment in an effort to ensure unbiased sampling. Trained research assistants will observe all processes of HIV screening and record time (in seconds) to complete each component. To estimate costs associated with performing

these interventions in an ED environment, we will also specifically include nights and weekends, and will specifically collect patient and staff data, stratified by study arm in order to ensure appropriate time measurements by intervention. Time per patient will be translated into time per month and per year, by position title, and position titles will be linked to median salary data from the Bureau of Labor Statistics for the respective metropolitan statistical area. See **Data Dictionary** and “**Time Motion Study Data Collection Instrument**” in the **Appendix**.

### Specific Aim 3

In this aim, we will collect additional ED process data in conjunction with patient enrollment as part of the clinical trial described in Specific Aim 1. We will include data from all patients enrolled in Specific Aim 1. Values for each of the four basic time metrics (patient waiting time, patient length of stay, patient boarding time, and proportion of patients who leave before completion of evaluation) will be collected real-time for all enrolled patients evaluated in each ED using electronic patient tracking systems. Patients who register for evaluation in each ED on a daily basis include time stamps related to initiation of medical screening, ED bed assignment, patient discharge or admission to the hospital and, if admitted to the hospital, inpatient bed assignment. The fifth metric, ED crowding, will be calculated using one of two validated ED crowding metrics (described in detail below). See **Data Dictionary** in the **Appendix**.

## **F. Outcome Measures**

### Specific Aim 1

Confirmed newly-diagnosed HIV infection will serve as our primary outcome. In anticipation of testing patients with previously diagnosed HIV infection (i.e., repeat diagnoses), our secondary outcome will include a composite of new diagnoses and repeat diagnoses.

Although confirmed newly-diagnosed HIV infection will serve as the primary outcome for this study, we believe important secondary effectiveness evaluations include disease state at the time of diagnosis as well as a longer-term evaluation of access to care, disease progression, and treatment. Therefore, additional outcomes will include behavioral risk information, CD4 count (cells/ $\mu$ L) and viral load (copies/mL) at the time of diagnosis, and successful linkage into care (defined as completion of an initial HIV clinic visit). Details of follow-up care and disease progression for a period of one year following diagnosis will also be collected, including the number of scheduled and unscheduled medical care visits, whether antiretroviral therapy and treatment for opportunistic infections were initiated, the number of hospitalizations, and mortality.

### Specific Aim 2

Programmatic costs associated with implementation of targeted and nontargeted rapid HIV screening strategies when fully-integrated into ED settings will be measured. We will estimate program costs using a simple cost allocation method that sums fixed and variable costs for program implementation. Components of costs by intervention arm will include: start-up, personnel, tests, supplies, and equipment. In order to estimate personnel-related costs by arm, time-motion data will be collected during randomly-selected time periods of the trial at each site (including different times of day and weekends). Personnel time spent per patient will be monetized by position title-specific median salary data from the Bureau of Labor Statistics for the respective metropolitan statistical area. Total programmatic costs, costs per person tested, and cost per HIV case detected will be compared by intervention arm. Differences across sites will be explored in sensitivity analyses. Uncertainty in cost estimates will be estimated using bootstrapping resampling methods.

### Specific Aim 3

Five specific metrics of ED patient throughput will be measured in this aim. All five measures are commonly thought to represent ED processes of care and crowding. The first metric, patient waiting time, will be defined as the time from initiation of medical screening by the screening nurse to the time the patient is assigned a bed in the ED. The second metric, patient length of stay, will be defined as the time from when the patient is assigned a bed in the ED to the time of discharge or, for those admitted to the hospital, the time an inpatient bed is requested by a physician. The third metric, patient boarding time, will be defined as the time from when an inpatient bed is requested to the time the patient leaves the ED for that bed. The fourth metric, proportion of patients who leave before completion of evaluation, will be defined as the proportion of all patients who either leave before being placed in a treatment room or leave before completion of their evaluation. The fifth metric, Emergency Department Work Index (EDWIN) or the National ED Overcrowding Score (NEDOCS), are global or composite crowding metrics and are defined as:

$$\text{EDWIN} = \sum n_i t_i / N_a (B_T - B_A),$$

where  $n_i$  = the number of patients present in the ED by triage category ( $i$ );  $t_i$  = the acuity category (defined using an ordinal scale from 1 to 5, 1 being the most acute and 5 being the least acute);  $N_a$  = the number of physicians on duty at a given time;  $B_T$  = the total number of beds available in the ED; and  $B_A$  = the number of admitted patients waiting for inpatient bed assignment in the ED. The EDWIN metric can range from 0 to infinity, and a previous validation study demonstrated median EDWIN scores of 1.1 (IQR: 0.8 – 1.6), 1.6 (IQR: 1.2 – 1.9), and 1.8 (IQR: 1.4 – 2.5) during non-busy, average, and busy ED time periods, or

$$\text{NEDOCS} = -20 + 85.8(\text{total ED patients} \div \text{total ED beds}) + 600(\text{boarded patients} \div \text{total hospital beds}) + 13.4(\text{number of ventilated patients in the ED}) + 0.93(\text{longest boarder time in hours}) + 5.64(\text{longest time for patient waiting in hours})$$

where 0 – 20 is considered “not busy”, 21 – 60 considered “busy”, 61 – 100 considered “very busy”, 101 – 140 considered “crowded”, 141 – 180 considered “dangerous”, and 181 or greater considered “disaster”. EDWIN and NEDOCS have been compared head-to-head and have both been shown to be valid and comparable metrics for quantifying ED crowding.

Values for each of the four basic time metrics will be collected real-time for all patients enrolled into the study using electronic patient tracking systems. Patients who register for evaluation in each ED on a daily basis include time stamps related to initiation of medical screening, ED bed assignment, patient discharge or admission to the hospital and, if admitted to the hospital, inpatient bed assignment. Because EDWIN and NEDOCS rely on point-in-time sampling and at the level of the ED, it is not feasible to measure their variables on a continuous, real-time basis. However, we will calculate the fifth ED metric, either EDWIN or NEDOCS, at the time each patient begins medical screening and when he or she is discharged. The difference between these data will be used as a covariate in the analyses for this aim as described below.

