Process metric variables for all enrolled patients will be compared between study arms. Because the time and EDWIN or NEDOCs metrics are continuous, they will be reported as means with SDs or medians with IQRs. Bivariate analyses will be used to estimate statistical differences between each process metric and the three HIV screening interventions. Because we propose measuring five ED process metrics, we have defined statistical significance for this part of the analyses to be a Bonferroni-adjusted p-value <0.01. Also, hierarchical multivariable linear regression analyses will also be used to estimate associations between each of the interventions and continuous process metrics, while accounting for clustering at the institution level and adjusting for overall ED crowding as measured by the difference in either EDWIN or NEDOCs for the duration of the patient's visit. If necessary, continuous data will be transformed and multiple imputation will be used in instances where data are missing. The primary unit of analysis will be patient visits.

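### The EDWIN crowding score gives the most acute patients the smallest weight, so at a fixed census, staffing and bed supply it falls as the patient mix becomes sicker

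*Protocol*

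**What the plan says.** Protocol section 4.F (Outcome Measures, Specific Aim 3) allows either EDWIN or NEDOCS as the fifth metric of ED throughput. EDWIN is the sum over triage categories of n_i × t_i, divided by N_a × (B_T − B_A). Here n_i is the number of patients in category i, N_a is "the number of physicians on duty at a given time", B_T is "the total number of beds available in the ED" and B_A is "the number of admitted patients waiting for inpatient bed assignment in the ED". The acuity value t_i runs from 1 to 5, with "1 being the most acute and 5 being the least acute".

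The section then cites median EDWIN values of 1.1, 1.6 and 1.8 "during non-busy, average, and busy ED time periods", so a higher score is meant to indicate a busier department. NEDOCS includes a term of +13.4 per ventilated patient. The section describes the two scores as valid and comparable.

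The score is used in two ways. Crowding is Hypothesis 3(e), and section 4.H (Analytic Plan, Specific Aim 3) compares the process metrics, including EDWIN or NEDOCS, between arms. The regression models for the continuous metrics also adjust for crowding "as measured by the difference in either EDWIN or NEDOCs" over the patient's visit.

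**The concern.** The acuity value is a multiplier in the numerator, and nothing in the text shown inverts it. As defined, the sickest patient counts least towards a quantity named a work index and used as a measure of crowding. Its acuity component also runs against NEDOCS, where the sickest patients push the score up, although the protocol lets either be used.

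A programmer who takes triage levels straight from the tracking system and follows this definition would produce a score that responds to acuity mix in the wrong direction. At stake are the fifth Aim 3 metric at the sites that choose EDWIN, the crowding covariate in the Aim 3 models, and the comparability of that covariate between EDWIN and NEDOCS sites.

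**Working it through.** **Can the cited medians be reproduced?** No. The protocol gives no census, acuity mix, physician count or bed count behind 1.1, 1.6 and 1.8. The check is therefore of direction, with illustrative inputs.

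**Reading of the formula.** EDWIN = Σ n_i t_i / [N_a (B_T − B_A)], taking the product of physicians and available beds as the denominator. The direction with respect to acuity does not depend on how the denominator is read.

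**General result.** Let t_i be the weight as written, t'_i = 6 − t_i the reversed weight, and n = Σ n_i. Then

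EDWIN' = Σ n_i (6 − t_i) / [N_a (B_T − B_A)] = 6n / [N_a (B_T − B_A)] − EDWIN.

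With n, N_a and B_T − B_A fixed, the first term is constant, so the two versions move in exactly opposite directions.

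**Moderate mixes.** Assumed: n = 30, N_a = 3, B_T = 30, B_A = 5, so the denominator is 3 × 25 = 75.

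| Patients in categories 1/2/3/4/5 | As written | Reversed |
|---|---|---|
| Sicker: 4/10/12/3/1 | (4+20+36+12+5)/75 = 77/75 = 1.03 | 180/75 − 77/75 = 103/75 = 1.37 |
| Less sick: 1/3/12/10/4 | (1+6+36+40+20)/75 = 103/75 = 1.37 | 180/75 − 103/75 = 77/75 = 1.03 |

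The ratio is 103/77 ≈ 1.34. If the department moves from the less sick to the sicker mix during a visit, the covariate is (77 − 103)/75 = −0.35 as written and +0.35 reversed.

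**Extreme mixes.** Assumed: n = 30, N_a = 5, B_T = 40, B_A = 10, so the denominator is 5 × 30 = 150. Ten patients in category 1 and twenty in category 2 give (10 + 40)/150 = 0.33. Twenty in category 4 and ten in category 5 give (80 + 50)/150 = 0.87. The ratio is 130/50 = 2.6, and the two values swap when the scale is reversed. The ratio does not depend on the denominator.

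**Census still counts.** With the denominator of 75, one more category 1 patient adds 1/75 = 0.013 and one more category 5 patient adds 5/75 = 0.067. Both are increases.

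**How far the two versions diverge.** Departments were simulated with mean census 30, a denominator of 75, and acuity mixes varying around 5/25/45/20/5 per cent (all assumed). The correlation between the two versions was −1.00 with census fixed, about 0.15 with a census SD of 3, and about 0.80 with a census SD of 8. The coding matters most where census varies little.

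**The case against.** The best defence is that census, staffing and boarding also drive EDWIN, and all three act in the intended direction as written: more patients, fewer physicians or more boarders raise the score. This stands. A reader might infer that the score falls whenever a department holds sicker patients, but that is true only with those quantities fixed.

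A reader might also infer that the cited medians contradict the definition, or were obtained on the opposite scale. The documents do not support this. The medians are ordered by busyness, not by acuity, and a score that rises with census fits them. Which scale the cited validation study used cannot be checked here.

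A third tempting inference is that the Aim 3 arm comparisons are biased. This is not shown. Patients are randomised 1:1:1 concurrently within each ED, and EDWIN is a department-level value shared by patients of all arms present at the time. Its value at screening is therefore balanced across arms in expectation, and one patient's assignment can hardly move it. The bivariate comparisons of the other four metrics do not use it.

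Nor can it be said that every EDWIN site will hold wrong values. The protocol does not say which sites use EDWIN, and the Data Dictionary to which section 4.E refers is not among the text shown and may code acuity differently.

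None of this defends the definition itself. It limits how much follows from it.

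**Conclusion.** The definition of t_i in section 4.F is wrong for a work and crowding index. At fixed census, physicians and available beds, the score falls as the mix becomes sicker, against the purpose of the index and against the acuity component of NEDOCS. That the scale was reversed in drafting is an inference from that purpose and from NEDOCS; the source of the index was not consulted.

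The size depends on assumed mixes: a ratio of about 1.3 for moderate ones, rising to 2.6 for extreme ones, which should not be taken as typical. If EDWIN is coded as written, the sites using it would mis-measure the fifth Aim 3 metric (Hypothesis 3(e)) and the within-visit covariate. The main consequences are poor adjustment for crowding and values that do not line up with NEDOCS. Aim 1, including the primary HIV outcome, is untouched.

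**What to change.** In section 4.F, define t_i so that the most acute category carries the largest weight, for example t_i = 6 − triage level where level 1 is the most acute. Confirm that direction against the cited index and the Data Dictionary. Check the derivation code at each site using EDWIN before any value is computed or set beside the cited medians.

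The cost is one line of protocol text and a code check. No new data are needed: by the identity above, any score already computed as written can be converted from the same census, physician and bed counts that produced it.
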